#### Inclusion Criteria (Practices)

• Practice keeps a register of patients with CHD for the Quality and Outcomes Framework (QOF) and is willing to liaise over patients in the case management arm when necessary

#### Inclusion Criteria (Participants)

• Symptomatic CHD as scored on the modified Rose Angina Questionnaire

• A score ≥8 on the depression part of the Hospital Anxiety and Depression Scale

• Aged 16 years or over

#### Exclusion Criteria (Participants)

• Temporary registrations

• Actively suicidal patients

• Psychotic depression as evidenced by delusions and/or hallucinations

• Non-English speaking

• Participants currently in hospital for treatment of their CHD

Up to 20 group practices of around 10,000 patients each from South London will be recruited by the Greater London Local Research Network (GLLRN) to participate in the study.

#### Intervention

The nature of the intervention will be determined by the results of the two qualitative studies.

#### Control

Participants randomised to the TAU control group will receive treatment as usual by their GP and any other relevant professionals.

#### Measures

Participants will be followed up at 1-, 6- and 12-months post randomisation. The same measures will be applied at each follow-up. The measures to be used are shown in Table 2.

**Table 2 T2:** Measures to be used at each time point in the pilot randomised controlled trial

Outcome Parameter	Instruments
	

*Primary Outcome*	

Depression	Hospital Anxiety and Depression Scale[22]

*Secondary Outcome*	

Depression	Patient Health Questionnaire-9 [24]

Coronary Heart Disease	Rose Angina Questionnaire[17], Guy's Hospital Chest pain Questionnaire[19], Specific Activity Schedule [20]

Quality of Life	Euroqol-5D [25], Medical Outcomes Survey Short Form-12 (SF-12) [18]

Adherence to medication	Adapted version of Morisky adherence questionnaire[35]

Life events	List of Threatening Events Questionnaire [26]

Social problems	Social Problems Questionnaire [27]

Health Service Utilisation	Client Service Receipt Inventory (CSRI) [28]

Illness Perceptions	Brief Illness Perceptions Questionnaire [29]

Wellbeing	Warwick-Edinburgh Mental Well-being Scale [36]

Participants problem priorities	PSYCHLOPS [37]

In order to evaluate the process of delivering the intervention, focus groups of participants in the intervention arm and primary care professionals will be conducted to explore their experiences, views on the intervention, and their experience of participating in this study.

#### Randomisation

The unit of randomisation will be the participant. Randomisation will be conducted independently by the Clinical Trials Unit at the Institute of Psychiatry, King's College London. Randomisation will be by random permuted blocks.

#### Blinding

Researchers will be blind to randomisation status. Researchers will be asked to give their opinion on randomisation status at the end of the study to determine whether blinding was adequate.

#### Statistical analysis

Descriptive analyses will be used to provide summary estimates of outcome measures, focussing on the dropout rate at each time point, the order of magnitude of the effect of the intervention and the variability of the outcome measure at baseline. T-tests and regression modelling will be used to test whether there is a statistically significant difference between intervention and control groups. All analyses will be by intention to treat. While the sample size will not be sufficient to test clustering effects formally, sources of clustering will be identified so that they can be taken into account in a definitive RCT.

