## Study 4: Feasibility study for a randomised controlled trial of case management for depression in primary care patients with symptomatic coronary heart disease

### Objectives

The objectives of this pilot are:

1. *Clinical efficacy of case management*

To explore whether case management for primary care patients with symptomatic coronary heart disease and depression, when delivered by mental health professionals may be more effective than treatment as usual.

2. *Sample size calculation*

Estimates of the location of the mean and variability around the mean (standard deviation) for the primary outcome measure (see measures) will be calculated. A conservative estimate using the 95% upper confidence limit will be used to inform the sample size calculation of the definitive RCT.

3. *To enable selection of the most appropriate primary and secondary outcome measures*. The pilot will also allow potential secondary outcome measures to be assessed.

4. *Integrity of the study protocol*

The pilot will allow all procedures for a definitive effectiveness RCT to be piloted. This will include testing:

• inclusion/exclusion criteria

• training of staff in the administration and assessment of the intervention.

5. *Testing data collection forms and questionnaires*

This will ensure that the questionnaires are acceptable to the participants, are comprehensible, appropriate, clearly defined and presented in a consistent manner. Patient information documents and consent forms will also be tested. Inter-rater reliability between researchers will be tested.

6. *Randomization procedure*

The randomisation process and acceptability of randomisation to primary care professionals and participants will be tested.

7. *Recruitment and consent*

The recruitment method will be tested and the consent rate for participants into the study calculated. Barriers to recruitment of both practices and participants will be explored. Follow-up rates will be calculated.

8. *To determine the acceptability of the intervention and the trial to practices and participants*. To determine the possible sources of contamination, and to develop a standardised manual for case management for use in the definitive RCT. To make an informal assessment of the degree to which the intervention can be standardised and whether therapist effects are likely to be a major factor.

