#### Participant recruitment

All patients on practice case registers for CHD will be asked by their GP for consent to contact from a researcher. Those consenting will be contacted by a researcher and assessed for depression using the Patient Health Questionnaire-2[33] and for symptoms relating to CHD using the Modified Rose Angina Questionnaire [34]. Patients scoring 3 or more on the PHQ-2, and with symptomatic CHD will then be assessed further using the Hospital Anxiety and Depression Scale (HADS)[22]. If they score >9 on the depression scale of HADS they will be eligible to participate in the study. Those consenting to participate will then be randomised to either to the intervention (case management) or the treatment as usual (TAU) arm of the study.

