#### Sample size

If we want to show a mean difference between intervention and control of ≥ 3 on the HADS Depression subscale, assuming a standard deviation around mean scores of 4, we will need 30 participants per group for 90% power at the 95% significance level. Therefore 60 participants (30 per arm) will be recruited into the RCT.

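### The pilot ties outcome variability to baseline, where HADS-D is range-restricted by the entry cut-off; the definitive trial should be sized on a follow-up (or baseline-adjusted) SD.

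*Protocol article*

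**What the plan says.** Objective 2 of the pilot (Study 4, Objectives) is to supply planning figures for the definitive trial: "Estimates of the location of the mean and variability around the mean (standard deviation) for the primary outcome measure (see measures) will be calculated". It continues: "A conservative estimate using the 95% upper confidence limit will be used to inform the sample size calculation of the definitive RCT". No time point is given.

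The Study 4 Statistical analysis section does give one. Dropout is to be reported separately at every time point. The same sentence then lists "the order of magnitude of the effect of the intervention and the variability of the outcome measure at baseline".

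HADS is the primary outcome (Table 2), collected again at 1, 6 and 12 months. Its depression subscale also decides entry. Participant recruitment states: "If they score >9 on the depression scale of HADS they will be eligible to participate in the study". The inclusion criteria list: "A score ≥8 on the depression part of the Hospital Anxiety and Depression Scale". These two cut-offs contradict each other and must be reconciled; the point below applies to either.

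The pilot's own sample size targets "a mean difference between intervention and control of ≥ 3 on the HADS Depression subscale", "assuming a standard deviation around mean scores of 4".

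**The concern.** Selecting patients on a score narrows the spread of that score. If the screening HADS-D serves as baseline, nobody randomised can lie below the cut-off, so the baseline SD is restricted. Follow-up scores have no such floor and spread out again.

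The comparison of arms is made at follow-up. An unadjusted t-test needs the follow-up SD, and a baseline-adjusted regression needs the residual SD. The baseline SD among entrants is neither.

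The upper confidence limit in objective 2 allows for sampling error in whichever SD is estimated. It does not correct for estimating the wrong one. A definitive trial sized this way could be too small while its planning figure is described as conservative.

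**Working it through.** **1. The plan's own figure.** Inputs from the Sample size section: difference 3, SD 4, 90% power, 5% level, stated as "we will need 30 participants per group for 90% power at the 95% significance level". The formula is n per arm = 2(z_α + z_β)² SD² / difference².
- Two-sided: 2 × (1.960 + 1.282)² × 16/9 = 37.4, so 38 per arm (39 with the t-distribution).
- One-sided: 2 × (1.645 + 1.282)² × 16/9 = 30.4, so 31 per arm, with 89.6% power at 30.

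The stated 30 is therefore close to a one-sided calculation; two-sided, it gives about 82% power. Sidedness is not stated, which is a separate matter. Below I use two-sided 5% and the t-distribution.

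**2. Baseline SD among entrants.** The article gives no SD for eligible patients, so this step rests on assumptions: HADS-D before the cut-off is roughly normal on a 0 to 21 scale with SD 4 (the plan's figure), and the screening score is the baseline score.

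| Mean before cut-off | SD if ≥8 | SD if ≥10 (i.e. >9) |
|---|---|---|
| 5 | 1.98 | 1.70 |
| 7 | 2.31 | 1.97 |
| 10 | 2.83 | 2.43 |

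The range is about 1.7 to 2.8. Handling the ends of the scale differently changes these values only in the second decimal place.

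**3. Follow-up SD in the same people.** I further assume an unselected SD of 4 at follow-up and a baseline/follow-up correlation of 0.4 to 0.7. Simulation with selection on baseline only gives a follow-up SD of about 3.1 to 3.8. For means of 5 to 9, the ratio of baseline to follow-up SD is 0.46 to 0.78.

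**4. What the upper limit restores.** With n = 60, the one-sided 95% upper limit multiplies the SD by √(59/χ²₀.₀₅,₅₉) = √(59/42.34) = 1.18 (1.22 if two-sided). The ratio becomes 0.46 × 1.18 ≈ 0.55 to 0.78 × 1.18 ≈ 0.92, still below 1.

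**5. Example.** A baseline SD of 2.3 arises with mean 7 and cut-off ≥8, or mean 9 and cut-off ≥10.
- Planning SD: 2.3 × 1.18 = 2.7.
- Normal formula: 2 × (1.960 + 1.282)² × 2.714²/9 = 17.2. The t-based size is 18.2, so 19 per arm.
- Noncentrality at 19 per arm: 3/(SD × √(2/19)). For SD 3.1 this is 2.98 and for SD 3.8 it is 2.43, on 36 degrees of freedom.

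| SD relevant to the comparison | n per arm for 90% | Power at 19 per arm |
|---|---|---|
| 3.1 (low end, unadjusted) | 24 | 83% |
| 3.8 (high end, unadjusted) | 35 | 66% |
| 3.46 (adjusted, correlation 0.5) | 29 | 74% |
| 2.86 (adjusted, correlation 0.7) | 21 | 88% |

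The adjusted SD is 4√(1 − r²): 4√0.75 = 3.46 and 4√0.51 = 2.86. The 66% to 83% range spans all the follow-up SDs in step 3. In the two settings that give a baseline SD of 2.3, the follow-up SD is about 3.3 to 3.8, and power is 78% to 66%.

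**The case against.** **The link is an inference.** The strongest reply is that no sentence says the baseline SD will size the definitive trial. Objective 2 gives no time point and points the reader to the measures, where HADS is collected at three follow-ups. The analysis section promises summary estimates of outcome measures in general and lists baseline variability as a focus, without excluding follow-up SDs. This stands, and it is why the conclusion is conditional. It does not remove the point: baseline is still the only time point named for variability, in a sentence that takes care to report dropout at each one.

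**The size depends on assumptions.** This also stands.
- Patients reach the HADS only after a PHQ-2 score of 3 or more, so the mean before the cut-off may be higher. At mean 12 the baseline SD is about 3.1 to 3.2 (≥8) or 2.7 to 2.8 (≥10), and the upper limit then closes much or all of the gap.
- A flat spread of scores over 8 to 21 would give an SD of 4.0 and no restriction to speak of.
- The analysis section already plans regression modelling. With mean 9, cut-off ≥8 and correlation 0.7, the inflated baseline SD is 2.68 × 1.18 = 3.2, above the residual SD of about 2.9.

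**Stronger readings.** A reader might infer that the baseline SD is far too small and that power would fall to 61%. That figure needs an SD of 4 both before selection and at follow-up in the selected group. Under the model used here the follow-up SD is lower, so 61% overstates the loss. A reader might also infer that the upper limit could be applied to the mean or the treatment effect, or that the pilot mean will set the target difference. The limit follows directly on the mention of the SD, the ordinary reading is the SD, and nothing says the target will come from the pilot.

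**Conclusion.** The point holds in conditional form. The article attaches outcome variability to the one time point at which the entry criterion restricts it, and a stated aim of the pilot is to supply the SD for the definitive trial. If the baseline SD were carried forward, it would probably be too small for an unadjusted follow-up comparison, and the upper limit would not generally repair that.

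Under the stated assumptions (roughly normal scores, unselected SD 4, mean 5 to 10, correlation 0.4 to 0.7, screening score used as baseline), the worked example gives about 66% to 83% power where 90% was intended. With strong baseline adjustment the loss is small or absent. The documents do not allow a single figure. The pilot's own conduct, data and comparison are unaffected; what is at risk is the planning of the next trial.

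**What to change.** In the Study 4 Statistical analysis section, replace the baseline variability item with the pooled within-arm SD of HADS-D at the follow-up time point intended as primary, together with its correlation with baseline (or, equivalently for planning, the baseline-adjusted residual SD). Baseline SD can still be reported as a description of the sample.

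In objective 2, state that this is the SD whose upper 95% limit will be used for the definitive trial.

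Separately, reconcile the two HADS depression cut-offs in Participant recruitment and the inclusion criteria, since the degree of range restriction depends on which applies.

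The cost for the SD is one sentence in each of two sections. HADS is already collected at every follow-up, so no new data are needed.

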#### Setting and Practice recruitment

The study will be carried out in primary care. Practices in South London which are not participating in the cohort study will be recruited via the Greater London Primary Care Research Network (PCRN-GL) and invited to participate in the pilot study. We estimate from the results of the cohort study that we will need 10-15 practices each with around 10,000 patients in order to randomise between 30 and 50 participants per arm.

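### The pilot's HADS-D t-test and its power figure carry no case-manager component, so the interval is too narrow and power overstated if outcomes vary by case manager

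*Protocol article*

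**What the plan says.** All references are to Study 4 in the protocol article.

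- **Allocation and delivery.** The Randomisation section makes the participant the unit of randomisation. Objective 1 has mental health professionals deliver the intervention, and Ethical considerations refers to case managers in the plural. Under Control, the treatment-as-usual (TAU) arm is looked after by GPs and other relevant professionals. One arm is therefore nested in trial case managers and the other is not.
- **Sample size.** The target is a "mean difference between intervention and control of ≥ 3 on the HADS Depression subscale", "assuming a standard deviation around mean scores of 4", from which "we will need 30 participants per group for 90% power at the 95% significance level". Hence "60 participants (30 per arm) will be recruited into the RCT". No design effect appears. Setting and Practice recruitment plans enough practices "in order to randomise between 30 and 50 participants per arm".
- **Analysis.** "T-tests and regression modelling will be used to test whether there is a statistically significant difference between intervention and control groups". On clustering: "While the sample size will not be sufficient to test clustering effects formally, sources of clustering will be identified", for use in the definitive trial.
- **Therapist effects.** Objective 8 plans an informal assessment of "whether therapist effects are likely to be a major factor".

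The protocol gives no ICC, number of case managers or caseload. It does not say whether the regression models will carry a case-manager term.

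**The concern.** A two-sample t-test is not neutral about clustering: it sets the ICC to zero. Having too few data to test an ICC is no reason to assume that value. With few managers the assumption is hardest to check, and caseloads, and so the design effect, are largest.

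If some case managers get better results than others, patients who share a manager resemble each other. The variance of the intervention-arm mean then has a between-manager part that the t-test and the sample size omit. The error always runs the same way, towards too narrow an interval and too small a p-value. Part of what is reported as an effect of case management could be the effect of the particular people who delivered it.

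The comparison is more than a by-product of the pilot. HADS is the primary outcome, the sample size is justified by power for it, and the abstract promises evidence on efficacy as well as feasibility.

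**Working it through.** **Inputs from the protocol:** difference 3, SD 4, 30 per arm, 1:1, 5% level (sidedness not stated).

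**Assumed, because the protocol does not give them:** intervention-arm ICC ρ from 0.01 to 0.10; k = 2 to 6 managers with equal caseloads m = 30/k; total SD 4 in both arms.

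**Step 1: the plan's own figure, assuming independence.**

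SE = 4 × √(2/30) = 1.033, and 3/1.033 = 2.905.

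- One-sided 5%: power = Φ(2.905 − 1.645) = 89.6%. For 90%, n = 2 × 16 × (1.645 + 1.282)²/9 = 30.5, so 31 per arm. The stated figure is reproduced to within one patient per arm.
- Two-sided 5%: power = Φ(2.905 − 1.960) = 82.8% (81.5% by the noncentral t). For 90%, n = 2 × 16 × (1.960 + 1.282)²/9 = 37.4, so 38 per arm. The stated figure is not reproduced.

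The two-sided baseline for the effect of clustering is therefore 82.8%, not 90%.

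**Step 2: clustering in the intervention arm only.**

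- Design effect: DE = 1 + (m − 1)ρ
- Correct SE = 4 × √((DE + 1)/30)
- Ratio of correct to t-test SE: r = √((DE + 1)/2)
- True size of the nominal 5% two-sided test = 2 × (1 − Φ(1.96/r))
- Two-sided power with the correct SE = Φ(3/SE − 1.96)

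Worked example, k = 2 and ρ = 0.05: m = 15, DE = 1.70, SE = 4 × √(2.70/30) = 1.20, r = 1.162. Size = 2 × (1 − Φ(1.687)) = 9.2%. Power = Φ(2.50 − 1.96) = 70.5%.

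| Managers | ICC | DE | SE ratio | True size | Two-sided power |
|---|---|---|---|---|---|
| any | 0 | 1.00 | 1.000 | 5.0% | 82.8% |
| 6 | 0.01 | 1.04 | 1.010 | 5.2% | 82.0% |
| 4 | 0.02 | 1.13 | 1.032 | 5.8% | 80.4% |
| 4 | 0.05 | 1.325 | 1.078 | 6.9% | 76.9% |
| 3 | 0.05 | 1.45 | 1.107 | 7.7% | 74.7% |
| 2 | 0.05 | 1.70 | 1.162 | 9.2% | 70.5% |
| 2 | 0.10 | 2.40 | 1.304 | 13.3% | 60.6% |

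Simulating the unadjusted t-test (30,000 replicates per row) gave sizes within about 0.3 percentage points of the formula. On the one-sided basis that reproduces the stated 90%, power at ICC 0.05 is about 85%, 84% and 80% with 4, 3 and 2 managers.

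**Step 3: the upper recruitment figure.** With 50 per arm and the same number of managers, caseloads grow. At ICC 0.05 the formula gives a size of 12.1% with 2 managers (DE = 1 + 24 × 0.05 = 2.20) and 9.7% with 3. Recruiting more patients per manager makes the size error worse.

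**Step 4: degrees of freedom.** The powers above use normal critical values. A comparison based on manager means with Satterthwaite degrees of freedom, simulated at ICC 0.05 and 30 per arm, has power of about 50% with 2 managers and 59% with 3, against 70.5% and 74.7%. With so few managers the answer depends heavily on the degrees-of-freedom method, so that method has to be stated.

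**The case against.** **The limitation is disclosed and the aim is exploratory.** This is fair. Objective 1 only asks whether case management may be better, the analysis section leads with description, and therapist effects are to be looked at informally. Clustering was not overlooked. But disclosure serves the later trial; it does not widen the pilot's own interval, and a test is still planned and powered.

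**The regression models might include a case-manager term.** They might, and a condensed article may leave that to the full protocol or analysis plan. The t-test named beside them cannot include one, and the sample size has none.

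**Inference could be limited to the managers employed.** On that fixed-effects view the t-test is not anti-conservative, and variation between managers becomes a question of generalisability. This stands as a condition on the point.

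**Stronger readings that a reader might infer, which the documents do not support:**

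- That the p-value is certainly too small. This needs an ICC above zero, and at ICC 0.01 with 6 managers the inflation is negligible.
- That one manager carries the whole arm, which would give the worst figures. The protocol speaks of case managers in the plural.
- That the t-test was chosen because clustering cannot be tested. The section does not give that as its reason.
- That a falsely significant result would trigger the definitive trial. No section ties progression to the p-value, and the Background already treats that trial as necessary.
- That clustering explains the whole shortfall from 90% power. The step from 90% to 82.8% arises under independence.
- That practice clustering is balanced out because randomisation is within practice. Permuted blocks are specified, but stratification by practice is not mentioned.

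**Conclusion.** The point holds conditionally. As written, the t-test and the power statement set the case-manager ICC to zero in an arm that is nested by design. If outcomes vary by manager and the conclusion is meant to reach beyond those employed, the interval is too narrow and power is overstated.

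The size is uncertain because the ICC and the number of managers are assumptions. Over the range examined it runs from trivial (size 5.2%, power 82.0%) to serious (size 13.3%, power 60.6%). Nothing in the protocol rules out the serious end. For an exploratory pilot this does not threaten the design. It is worth correcting because the efficacy comparison will be read, and the correction is cheap.

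The 90% power figure needs restating on its own account if the test is two-sided.

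**What to change.** **In Statistical analysis:**

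1. Record each intervention participant's case manager and report the number of managers and their caseloads.
2. Present the HADS-D comparison as an estimated difference with an interval. Recompute the standard error at fixed intervention-arm ICCs, for example 0, 0.02, 0.05 and 0.10. Label these as assumptions and state the degrees-of-freedom method. A model that estimates the manager component is an option only with enough managers; with 2 or 3 the estimate would be unreliable.
3. State that any unadjusted p-value ignores case-manager clustering and is exploratory.

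**In Sample size:** say that the power assumes no case-manager clustering. Restate it, under independence at 30 per arm, as about 83% two-sided, or about 90% only if one-sided. Adding the clustering caveat alone would leave 90% standing as if it were correct two-sided.

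**Cost:** wording, and one data item that the trial already knows. No extra patients or staff. The price is a wider interval and a less favourable stated power. In return, the sensitivity table serves objective 8 and the design of the definitive trial.
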